#### Shoulder pain measurement

Shoulder pain will be evaluated through the NPRS scale. The participants will be asked to report their pain level on the NPRS (0–10 scale with 0 indicating no pain and 10 indicating the worst pain). The NPRS is a widely validated single 11-point numerical scale. The data obtained through NPRS is easily documented, intuitively interpretable, and meets regulatory requirements for pain assessment and documentation [21, 22].

#### Shoulder function measurement

Shoulder function will be evaluated using the SPADI questionnaire (Spanish validated version), which measures severity of upper extremity pain and disability during daily life activities [23]. This is a self-report questionnaire with 13 items on it (5 items specific to shoulder pain and 8 items specific to shoulder disability). The SPADI score can range from 0% indicating no pain or disability, to 100% indicating severe pain and total disability [24]. SPADI has been used previously in patients with DM [25, 26].

#### Shoulder’s range of motion (ROM)

The range of motion will be assessed through a digital inclinometer (Acumar™, Lafayette Instrument Company, Lafayette, IN). The inclinometer is reliable to measure the range of motion of shoulder flexion, abduction, scapular plane elevation, as well as internal and external rotation (ICC:0-85-0.97) [27]. For shoulder flexion, the arm should be actively elevated in a sagittal plane with the palm down until participants reach their full ROM, with the inclinometer placed on the distal upper arm proximal to the elbow, and distal to the glenohumeral joint. For shoulder abduction, the arm should be actively elevated in coronal plane with the thumb pointed upwards toward the ceiling until participants’ full ROM, with the inclinometer positioned on the distal arm proximal to the elbow, and distal to the glenohumeral joint. For shoulder elevation in scapular plane, participants will be instructed to perform elevation in scapular plane with the thumb pointing upwards toward the ceiling to full end range. The inclinometer will be positioned on the superior portion of the humeral shaft proximal to the elbow. To measure shoulder internal and external rotation, the participants will be in supine position with shoulder and elbow at 90° of abduction and flexion, respectively. The inclinometer must be placed on the distal dorsal surface of the forearm and the shoulder will be rotated actively in an internal and external rotation [28]. Three trials will be assessed for each movement.

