### Eligibility criteria {10}

#### Inclusion criteria

The inclusion criteria will be participants with a clinical diagnosis of type 2 DM (with at least 1 year of diagnosis), of both sexes, between 40 and 70 years old, presenting shoulder pain (unilateral or bilateral) for at least 3 months with a pain intensity score from 3 points on a numerical pain rating scale (NPRS).

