#### Exclusion criteria

Participants will be excluded if they present a history of shoulder surgery; recent history of fracture in the upper limb; cognitive deficits that make it difficult to understand verbal commands; neuromuscular diseases; central nervous system diseases; diagnosis of cardiovascular disease; kidney chronic disease and have undergone shoulder rehabilitation within the past 6 months

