#### Isometric shoulder muscles strength measurement

Isometric muscle strength of shoulder muscles will be assessed using a handheld dynamometer (HHD) (Lafayette Instrument, Lafayette, IN), a valid and reliable tool method (ICC = 0.94–0.97) [29–31]. Shoulder internal and external rotation strength will be evaluated following the protocol proposed by Kolber et al. [29], with the shoulder positioned in 0° of rotation, with the elbow positioned at a 90° of flexion and the wrist in neutral rotation. Shoulder flexion and abduction strength assessment will follow the protocol proposed by Çelik et al. [32] and Zanca et al. [33], respectively, with participants seated and the arm at 90° of elevation on a sagittal and scapular plane (30° anterior to the coronal plane). The dynamometer will be positioned in the distal humerus. Three repetitions of 5 s will be performed for each movement, with 30 s of rest between repetitions. A familiarization trial of each movement will be performed before data collection, to guarantee the participants’ comprehension [33]. The peak force (N) will be recorded for each trial and the mean of the three repetitions will be used for data analysis.

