#### Shoulder three-dimensional kinematics measurement

Shoulder three-dimensional kinematics will be recorded during maximal arm elevation in the scapular plane and during the following functional tasks: hand to head (brush the hair), hanging clothes overhead, eating, and reaching an object overhead (at 120°). Each measurement will be repeated three times with 60-s intervals, following the protocol of Dogan et al. [34], using an inertial movement unit’s system (IMU system) consisting of a 3D accelerometer, a 3D gyroscope, and a 3D magnetometer (MVN AWINDA Starter Wireless, Xsens Technologies B.V. Enschede, Netherlands), which is already validated in the literature to measure 3D shoulder kinematics [35]. Eight sensors will be used and placed on the anterior sternum, on the back of the head, on the lateral aspect of the bilateral arms, on forearms and on wrists. Measurements were evaluated for individuals in an anatomical position, performing activity, and then returning to the anatomical position. Each measurement was repeated three times with 60-s intervals. The mean values of kinematic data determined each individual’s functional ROM of joints. The joint angle definitions followed by the International Society of Biomechanics [36]. Data processing will be performed through the MVN Analyze software (Xsens Technologies B.V. Enschede, Netherlands), and the MATLAB® software will be used for data processing (R2015b, Mathworks Inc., Natick, MA USA), considering all of the shoulder’s functional range of motion movements (flexion/extension; internal/external rotation; abduction/adduction).

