### Methods in analysis to handle protocol non-adherence and any statistical methods to handle missing data {20c}

The study will include only participants who attended at least 80% of the sessions and performed all the assessments (per-protocol). Furthermore, missing data will be handled by intention-to-treat analysis using the multiple imputation method.

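### Two rotation range and two strength tests require 90° with no rule for shoulders that cannot reach it, and one sentence of {20c} would then remove self-reported SPADI data

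*Protocol article*

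**What the plan says.** All references are to the protocol article.

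- **Test positions.** In Shoulder's range of motion, for internal and external rotation, "the participants will be in supine position with shoulder and elbow at 90° of abduction and flexion, respectively". In Isometric shoulder muscles strength measurement, flexion and abduction strength are taken "with participants seated and the arm at 90° of elevation on a sagittal and scapular plane". Neither section gives an alternative position or a score for a participant who cannot reach the position.
- **Who can enter.** The inclusion criteria ask for participants "presenting shoulder pain (unilateral or bilateral) for at least 3 months with a pain intensity score from 3 points" on the NPRS, with no minimum range of motion. The shoulder-related exclusions are prior surgery, recent upper-limb fracture and rehabilitation within 6 months; adhesive capsulitis is not among them. The Background describes limited joint mobility as a usual finding in this population and names adhesive capsulitis as one of its disorders.
- **Who is analysed.** Section {20c} first says: "The study will include only participants who attended at least 80% of the sessions and performed all the assessments (per-protocol"). Its second sentence says that missing data are handled by an intention-to-treat analysis with multiple imputation.
- **What the primary outcome needs.** SPADI (primary) and NPRS (secondary) are self-reported and need no arm position. Range of motion and strength are listed among the other outcomes in {12}.

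**The concern.** A participant whose shoulder cannot be brought to 90° has no value for rotation range, flexion strength or abduction strength. Under the first sentence of {20c}, that gap means that not all assessments were performed, and the participant leaves the study analysis. Completed SPADI and NPRS questionnaires go too. The exclusion would be driven by shoulder severity, which SPADI also measures. When it arises after randomisation, it can also be driven by the treatment under test.

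The second sentence of {20c} points the other way, so the document does not settle whether such a participant is removed or imputed. Imputation is not a clean answer for the four tests themselves. Standard multiple imputation assumes data missing at random, but these values are missing because the shoulder is too stiff or painful. Imputing them from more mobile participants would tend to give the stiffest shoulders values that are too favourable.

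**Working it through.** **1. Which measures are affected.** Of five range-of-motion movements, two (internal and external rotation) require 90° of abduction. The other three go to the participant's own limit; for flexion, "the arm should be actively elevated in a sagittal plane with the palm down until participants reach their full ROM". Of four strength tests, two (flexion and abduction) require 90° of elevation. Rotation strength is described at 0° of rotation with no elevation angle. That makes four of nine measures.

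**2. When the inability occurs.** Under {16c}, the allocation envelope is opened after the baseline assessments. Inability at baseline therefore cannot depend on the arm, and removing those participants mainly narrows the sample. Inability at week 12 or 20 comes after allocation and can depend on it.

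**3. How post-randomisation removal biases SPADI.** In an arm with true mean μ, let a share p be untestable, with SPADI higher (worse) by Δ than the testable participants. Then μ = m + pΔ, where m is the mean of those kept, so m = μ − pΔ. With a common Δ:

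kept difference (SAG − SRG) = true difference + Δ(p_SRG − p_SAG).

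The bias is zero only if the two shares are equal. Illustration, assuming Δ = 16.8 (the design difference in {14}, used only for scale) and a true difference of −16.8:

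| p_SRG | p_SAG | Bias | Kept difference |
|---|---|---|---|
| 20% | 10% | 16.8 × 0.10 = 1.68 | −15.12 |
| 30% | 10% | 16.8 × 0.20 = 3.36 | −13.44 |

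If aerobic exercise frees shoulders, the rule hides 10% to 20% of the effect in these examples. If the shares run the other way, the rule inflates the effect by the same amount.

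**4. The plan's sample size.** Section {14} gives 16 per group, raised for 20% withdrawals to 20 per group. 16/(1 − 0.20) = 20, and 16 × 1.20 = 19.2, which rounds up to 20. That step reproduces. The 16 itself cannot be reproduced because no SD is stated. Solving a two-sided t-test backwards (16.8 points, 80% power, 5% alpha) gives an SD of about 15.9 to 16.4; 16.4 is used below.

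**5. Power if the literal rule applied.** The share lost solely to an untestable position is an assumption. Number per arm = 20 × (1 − share), or 20 × 0.80 × (1 − share) if the planned withdrawals also occur.

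| Assumed share | Only loss: n per arm, power | With 20% withdrawals: n per arm, power |
|---|---|---|
| 0% | 20, 0.88 | 16.0, 0.80 |
| 10% | 18, 0.85 | 14.4, 0.75 |
| 20% | 16, 0.80 | 12.8, 0.70 |
| 30% | 14, 0.74 | 11.2, 0.64 |

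**The case against.** The strongest reply is that {20c} also promises intention-to-treat with multiple imputation, under which nobody is removed. The affected tests are neither primary nor secondary outcomes. The number affected is unknown, and a rule for tests that cannot be done may sit in a full protocol, assessor manual or SAP that is not shown. The rotation section also does not say that 90° must be reached actively, so limited active elevation alone does not prove that a participant cannot be placed there.

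Much of this stands, and it limits the point. A reader might go further in several ways that the documents do not support:

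- **That stiff participants are certainly dropped.** This follows from only one of two conflicting sentences.
- **That the largest gains, those crossing 90°, go uncounted.** Flexion, abduction and scapular-plane range are recorded to the participant's own limit at each visit, and so is maximal elevation in the kinematics.
- **That the 120° overhead reach or the Crass ultrasound position adds to the problem.** The kinematics section does not say that a short reach yields no value, and the ultrasound section gives no elevation angle.
- **That the withdrawal allowance is used up at baseline.** Baseline inability is visible before allocation, and no share is given.
- **That the test positions should be changed.** This is a measurement trade-off. With no range floor at entry, no angle that every participant can hold is defined.

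What the reply does not remove is the written rule. A restriction to participants with every assessment is stated in this document, it conflicts with the sentence beside it, and imputation at random suits these four tests poorly.

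**Conclusion.** The point holds in limited form. Four other-outcome measures have a fixed 90° position with no fallback, and the entry criteria admit shoulders that may not reach it. That some will not is an inference from the stated limited mobility and unexcluded capsulitis; the documents give no distribution of range. The first sentence of {20c} would carry that inability over to SPADI and NPRS, and the second contradicts it.

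The main risk is selection after randomisation at weeks 12 and 20. Its size depends on the difference in untestable shares between arms: about 1.7 to 3.4 SPADI points under the illustrative assumptions, and nil if the shares are equal. The power loss, to about 0.75 to 0.64 from 0.80, rests on an assumed 10% to 30% loss, a back-solved SD and a two-sided t-test. If the intention-to-treat sentence governs, SPADI is protected and only the handling of the four tests remains open.

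**What to change.** 1. Reconcile the two sentences of {20c}. State that all randomised participants with SPADI data are in the primary analysis, and that failure to perform one physical test never removes a participant from SPADI, NPRS or any other outcome.
2. On the assessment form, record inability to reach the test position because of pain or stiffness as a result, distinct from a missed assessment.
3. For rotation range and for flexion and abduction strength only, analyse that result as the worst rank at the visit concerned, for example with the Mann-Whitney test already named in {20a}. Do this at least as a sensitivity analysis to multiple imputation.

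The cost is a few lines of text and one extra field on the form, with no added visits or staff. The downside is small: where the rank analysis replaces the mixed ANOVA for these four measures, it compares arms visit by visit and does not give the group-by-time model.

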#### Isometric shoulder muscles strength measurement

Isometric muscle strength of shoulder muscles will be assessed using a handheld dynamometer (HHD) (Lafayette Instrument, Lafayette, IN), a valid and reliable tool method (ICC = 0.94–0.97) [29–31]. Shoulder internal and external rotation strength will be evaluated following the protocol proposed by Kolber et al. [29], with the shoulder positioned in 0° of rotation, with the elbow positioned at a 90° of flexion and the wrist in neutral rotation. Shoulder flexion and abduction strength assessment will follow the protocol proposed by Çelik et al. [32] and Zanca et al. [33], respectively, with participants seated and the arm at 90° of elevation on a sagittal and scapular plane (30° anterior to the coronal plane). The dynamometer will be positioned in the distal humerus. Three repetitions of 5 s will be performed for each movement, with 30 s of rest between repetitions. A familiarization trial of each movement will be performed before data collection, to guarantee the participants’ comprehension [33]. The peak force (N) will be recorded for each trial and the mean of the three repetitions will be used for data analysis.

#### Shoulder three-dimensional kinematics measurement

Shoulder three-dimensional kinematics will be recorded during maximal arm elevation in the scapular plane and during the following functional tasks: hand to head (brush the hair), hanging clothes overhead, eating, and reaching an object overhead (at 120°). Each measurement will be repeated three times with 60-s intervals, following the protocol of Dogan et al. [34], using an inertial movement unit’s system (IMU system) consisting of a 3D accelerometer, a 3D gyroscope, and a 3D magnetometer (MVN AWINDA Starter Wireless, Xsens Technologies B.V. Enschede, Netherlands), which is already validated in the literature to measure 3D shoulder kinematics [35]. Eight sensors will be used and placed on the anterior sternum, on the back of the head, on the lateral aspect of the bilateral arms, on forearms and on wrists. Measurements were evaluated for individuals in an anatomical position, performing activity, and then returning to the anatomical position. Each measurement was repeated three times with 60-s intervals. The mean values of kinematic data determined each individual’s functional ROM of joints. The joint angle definitions followed by the International Society of Biomechanics [36]. Data processing will be performed through the MVN Analyze software (Xsens Technologies B.V. Enschede, Netherlands), and the MATLAB® software will be used for data processing (R2015b, Mathworks Inc., Natick, MA USA), considering all of the shoulder’s functional range of motion movements (flexion/extension; internal/external rotation; abduction/adduction).

#### Supraspinatus tendon thickness measurement

Ultrasonographic measurement for each participant’s supraspinatus tendon thickness will be scanned by using a Lumify Ultrasound in conjunction with a 4–12-MHz linear transducer (Philips Medical System) on musculoskeletal program. The protocol of the ultrasound measurement will be designed by an experienced sonographer in musculoskeletal ultrasound scanning. All ultrasound scanning will be performed by the researcher responsible of the study. Ultrasound images will be captured with the patients seated in an upright position, feet flat on the floor, neutral trunk posture, and head facing forward, evaluating supraspinatus tendon thickness in transverse and longitudinal, using both crass position and modified crass position [37–40]. The averaged value from the 3 measurements will be recorded as the supraspinatus tendon thickness.

#### AGE accumulation measurement

Skin autofluorescence is considered as a substitute variable of AGE accumulation. To perform this measurement, the AGE Reader (DiagnOptics, Groningen, the Netherlands) will be used, which non-invasively assesses skin autofluorescence. For this evaluation, participants will lay their arm on a special arm rest with a window in the middle of the AGE reader. A skin surface of around 4 cm^2^, guarded against surrounded light is illuminated with an excitation light source with LEDs of various intensities in a frequency range of 300 to 420 nm. Multiple photo diodes capture the auto fluorescent light, processes it, and generates the SAF (skin auto fluorescence) in arbitrary units (AUs). The resultant SAF is calculated as the ratio of the light intensity in a 420–600 nm wavelength range, and the light intensity in a 300–420 nm wavelength range. The assessment will follow the Meerwaldt et al. [41, 42] protocol. SAF measurements have been validated against biochemical analyses of skin biopsies in healthy participants, and in participants with type 1 or type 2 DM [25]. In participants with DM, SAF has an intra-individual, intra-day variability of 4.2–5.0%, and a seasonal variability of 5.9% [41, 43]. According to De Ranitz-Greven et al. [44], no increases were found in SAF postprandial, therefore a fasting measurement is not mandatory.

#### HbA1c (hemoglobin a1c), fasting glucose and lipid profile

HbA1c, fasting glucose, and lipid profile will be evaluated through blood tests that will be performed in a clinical laboratory, at the beginning (before starting the treatment protocol), after the 12-week intervention (3–7 days after the last session).

#### Global rating of change score

To evaluate the post-treatment results, focusing on the changes perceived by the participants.

### Plans to promote participant retention and complete follow-up {18b}

Researchers will be in contact with the participants during the study, through a telephone messenger group app, to solve doubts and share information. The participants will also be contacted by phone, twice/month to ask about their health status and to reinforce their participation.

### Data management {19}

Participants will receive a code number at the beginning of the study, which will be added in an excel file with all their personal information and measurements collected and analyzed (MFQ or RC), double checked (GZ, AC, or BS), and stored by the leading researcher (FHZ), protected with a password. Generated consents will be stored for 5 years after the end of the study, which will be discarded thereafter.

### Confidentiality {27}

The data collected can only be accessed by the responsible researcher and the other researchers (co-authors). Participants will receive a code number at the beginning of the study, only known by the responsible researcher, and will always maintain their anonymity in their study environment. All the data will only be used for academic purposes.

### Plans for collection, laboratory evaluation, and storage of biological specimens for genetic or molecular analysis in this trial/future use {33}

Not applicable, this study does not have biological specimens.

## Statistical methods

### Statistical methods for primary and secondary outcomes {20a}

Data will be analyzed using SPSS, version 20.0 (SPSS Inc. 233 S. Wacker Drive, Illinois USA). The statistical assumptions for all the tests will be assessed. In case of normality, to verify the effectiveness of protocols over time (12 weeks and follow-up of at week 20), a mixed model analysis of variance (ANOVA) with Bonferroni adjustment will be performed for pairwise comparisons. Variables that do not meet the ANOVA assumptions will be analyzed by the Mann-Whitney and Wilcoxon tests with Bonferroni correction a priori.

To assess the secondary objective of the study, Pearson’s or Spearman coefficient correlation, when applicable, and a linear regression analysis will be performed to assess the association between AGE accumulation and outcome measures.

The significance level will be set at 5% for all statistical analyses. Furthermore, the effect size will be calculated using the Cohen coefficient *d*.

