### Outcomes {12}

The results will be evaluated at 3 points: (1) baseline (before starting the intervention program), (2) after 12 weeks of intervention (after 48 h to 1 week from the last intervention), and (3) at the week 20 (follow-up). Regarding the outcomes, the shoulder assessed by the SPADI (Shoulder Pain and Disability Index) questionnaire will be considered as primary outcome; the secondary outcome will be shoulder pain, measured with NPRS scales. Other outcomes will include range of motion, measured using a digital inclinometer; isometric shoulder muscle strength, measured using a manual muscle dynamometer; shoulder kinematics, measured using three-dimensional inertial units measurement; supraspinatus tendon thickness, measured using an ultrasound; AGE accumulation, using a skin autofluorescence measurement; and HbA1c (hemoglobin a1c), fasting glucose and lipid profile measured by a simple blood test.

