### Participant timeline {13}

#### Sample size {14}

Sample size calculation was performed through the GPower software (version 3.1). The calculation was based on the study by Schmitt et al. [20], using the main outcome (SPADI questionnaire) to detect a mean difference of 16.8 points, considering a power of 80% and an Alfa of 5%. The sample size suggested was 16 per group; however, to account for possible withdrawals that may occur in this type of study, it will be increased by 20%, thus totaling 40 participants (20 per group).

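### The planned SPADI analysis does not adjust for baseline SPADI, and leaves open both the role of baseline and the term that tests superiority; the cost is precision, not bias

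*Protocol article*

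**What the plan says.** All references are to the protocol article.

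- **Outcomes {12}:** the SPADI "questionnaire will be considered as primary outcome". On timing: "The results will be evaluated at 3 points: (1) baseline (before starting the intervention program), (2) after 12 weeks of intervention", and the third point is week 20. Intervention description {11a} gives the same three visits, so every participant should have a baseline SPADI.
- **Statistical methods {20a}:** the stated aim is "to verify the effectiveness of protocols over time (12 weeks and follow-up of at week 20"), and for this "a mixed model analysis of variance (ANOVA) with Bonferroni adjustment will be performed for pairwise comparisons". Variables that fail the ANOVA assumptions go to Mann-Whitney and Wilcoxon tests with Bonferroni correction. Cohen's d is to be calculated. No baseline covariate is named for any of these. "The significance level will be set at 5% for all statistical analyses".
- **Sample size {14}:** the trial is sized "to detect a mean difference of 16.8 points" on SPADI, "considering a power of 80% and an Alfa of 5"%. This gives 16 per group, raised to 20 per group (40 in total) for withdrawals. No SD, sidedness or correlation is given.
- **Sequence generation {16a}:** allocation is 1:1, and no stratification is described.

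**The concern.** In a trial of 16 to 20 patients per arm, the baseline value of the primary outcome is usually the most useful covariate available, and here it costs nothing to obtain. A per-visit comparison that ignores it leaves chance baseline imbalance in the estimate. A change-from-baseline contrast removes the imbalance but over-corrects unless r is close to 1. An analysis of covariance (ANCOVA) has a variance no larger than either.

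A second gap adds to this. A group by time ANOVA offers a group main effect, a group by time interaction and pairwise contrasts. These answer different questions and can differ widely in power. The section names none of them as the test of superiority, and its wording leaves open whether the time factor has two levels (weeks 12 and 20) or three (baseline as well). At stake are the width of the interval around the SPADI difference and the clarity of the primary result.

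**Working it through.** **Inputs.** From Sample size {14}: difference 16.8 points, power 80%, alpha 5%, 16 per group, 20 per group after inflation. Assumed, because not stated: a two-sided test, equal SD at all visits, and the same correlation r = 0.3, 0.5 or 0.7 between any two visits. The overall tests further down also assume the full 16.8-point effect at both weeks 12 and 20.

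**The plan's own figure.** Without an SD, 16 per group cannot be recomputed, only back-solved. A two-sided t-test with 16 per group reaches 80% power at d = 1.024, so SD = 16.8 / 1.024 = 16.4. (A one-sided test would allow an SD of up to 18.7.) The inflation step reproduces: 16 / 0.8 = 20.

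**Variance of the week-12 contrast**, in units of 2·SD²/n:
- unadjusted: 1
- change from baseline: 2(1 − r)
- baseline-adjusted (ANCOVA): 1 − r²

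| | r = 0.3 | r = 0.5 | r = 0.7 |
|---|---|---|---|
| ANCOVA, 1 − r² | 0.91 | 0.75 | 0.51 |
| Unadjusted / ANCOVA, 1/(1 − r²) | 1.10 | 1.33 | 1.96 |
| Change / ANCOVA, 2/(1 + r) | 1.54 | 1.33 | 1.18 |

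**Analytic power of the week-12 contrast**, SD 16.4 (noncentral t; one degree of freedom fewer for ANCOVA):

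| | r = 0.3 | r = 0.5 | r = 0.7 |
|---|---|---|---|
| 16 per arm, unadjusted | 80% | 80% | 80% |
| 16 per arm, change | 66% | 80% | 95% |
| 16 per arm, ANCOVA | 83% | 90% | 97% |
| 20 per arm, unadjusted | 88% | 88% | 88% |
| 20 per arm, change | 76% | 88% | 98% |
| 20 per arm, ANCOVA | 91% | 95% | 99% |

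Simulated ANCOVA power (20,000 trials per setting) is within about a point of these: 82%, 88%, 97% at 16 per arm and 90%, 95%, 99% at 20.

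**Overall ANOVA terms if baseline is a third level** (simulated). The group main effect averages (0 + 16.8 + 16.8) / 3 = 11.2 points.

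| | r = 0.3 | r = 0.5 | r = 0.7 |
|---|---|---|---|
| 16 per arm, group main effect | 73% | 63% | 56% |
| 16 per arm, group × time (2 df) | 70% | 84% | 97% |
| 20 per arm, group main effect | 83% | 73% | 65% |
| 20 per arm, group × time (2 df) | 81% | 92% | 99% |

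**Overall ANOVA terms if only weeks 12 and 20 are levels.** Nothing is diluted. The group main effect has 94%, 90% and 86% power at 16 per arm. The group by time term has only 5%, its type I error rate, because a constant effect produces no interaction. The like-for-like comparison is the mean of the two visits with and without baseline as covariate: relative variance (1 + r)/2 = 0.65, 0.75, 0.85 unadjusted, against (1 + r)/2 − r² = 0.56, 0.50, 0.36 adjusted. That is 14%, 33% and 58% less variance, and power rises to 96%, 98% and 99.7%.

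**Validity.** Under no effect (16 per arm, r = 0.5) the simulated type I error is about 5% for the overall tests, the single-visit contrasts and ANCOVA alike.

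**The case against.** A reader might infer that the plan definitely treats baseline as a third outcome level and so dilutes the treatment effect to 11.2 points. The document does not support that. Its parenthesis names only weeks 12 and 20. Three levels is the usual set-up, and it fits a hypothesis in Objectives {7} worded as decreases and increases, but it remains an inference. Even then, dilution affects only the group main effect, which the section never names as the superiority test. The group by time term and change contrasts are not diluted, and at r = 0.7 the interaction has about the same power as a week-12 ANCOVA (97% each at 16 per arm).

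Nor does it hold that every available test is inefficient or misses the quantity used for sizing. If only weeks 12 and 20 are levels, the two-visit group main effect beats a single-visit ANCOVA at r = 0.3 (94% against 82%) and about matches it at r = 0.5. The planned pairwise comparisons can estimate a between-arm SPADI difference at a visit. At 20 per arm the unadjusted week-12 contrast has 88% power, above target. All of this stands.

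It can also be said that covariates are often left to an analysis plan, and that this is a condensed article. That carries weight for model detail. It carries less here, because the article commits to specific methods and none of them includes baseline. What survives is narrower: on either reading, adding baseline to the same contrast lowers its variance at every r examined.

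**Conclusion.** The point holds as a matter of precision and clarity. The stated SPADI analysis makes no baseline adjustment, and neither the role of baseline nor the deciding term is fixed. Chance imbalance under randomisation adds variance; it does not bias the estimate or inflate type I error.

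The gain from adjustment at week 12 is small if r is 0.3 (about 3 percentage points of power at either arm size) and substantial if r is 0.7 (17 points at 16 per arm, 11 at 20). The drop to 11.2 points, with power of about 73%, 63% and 56% at 16 per arm, is conditional on two things the document does not say: that baseline is a level, and that the group main effect is the test.

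The percentages rest on an assumed r, equal SDs, a two-sided test and a back-solved SD of 16.4. The direction of the gain does not depend on the SD. The change is worth making because it is cheap and the trial is small, not because the planned analysis is invalid.

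**What to change.** In Statistical methods {20a}:

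1. Analyse SPADI at weeks 12 and 20 as the outcomes in a linear mixed model with group, visit, group × visit, baseline SPADI and baseline SPADI × visit. A separate ANCOVA per visit is an acceptable simpler form.
2. State that baseline enters as a covariate and not as a level of time.
3. Name the baseline-adjusted between-group difference in SPADI at week 12 as the superiority test. Report it with a 95% CI, so that it can be read against the 16.8 points used for sizing; give week 20 from the same model.
4. Use the same model for NPRS and the other continuous outcomes that have a baseline value. Outcomes measured only at baseline and after 12 weeks, such as HbA1c, need only the week-12 ANCOVA.

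The cost is analysis wording. No new data, visits or participants are needed, and the SPSS package already named can fit the model.
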